### Oversight and Monitoring

A steering committee will be established comprised of all central study team members, older adults from the community, and partners from the YMCA. The steering committee will review study progress and monitor recruitment, data quality and completeness, and general study conduct. The steering committee will monitor the rate of adverse events and will be responsible for the dissemination of results and will meet every 6 months. Given that this trial presents minimal risks, we will not have a data monitoring committee.

We do not anticipate any safety risks to the participants. However, it is possible that they might experience muscle stiffness, soreness, falls, or injuries. Since the interventions will be delivered remotely, each participant will provide the name and telephone number of a friend or family member that the research staff can contact should the participant be alone at home and an emergency arises. If the adverse event is deemed to be the result of the intervention, an Adverse Event Form will be completed by a member of the trained research staff and appropriate medical attention will be sought as necessary.

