### Outcomes

Demographic information (birth date, sex, gender, marital status, living accommodation, employment status, education, ethnic origin, and household income) and comorbid conditions (identified using the Self-Administered Comorbidity Questionnaire) [55] will be collected at baseline. Primary and secondary outcomes will be assessed virtually at baseline, 12 weeks, 24 weeks, and 36 weeks. Health care usage data will be collected during follow-up assessments only.

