#### Health Care Usage

Health care usage data to assess service use and cost effectiveness of the trial will be collected using administrative data accessible at the Institute for Clinical Evaluative Sciences (ICES) at McMaster University. Specifically, usage data will be obtained through the following databases: Ontario Health Insurance Plan, National Ambulatory Care Reporting System, and the Discharge Abstract Database, which are all housed at ICES McMaster. We will use standard person-level costing approaches established by ICES [89] to capture the formal component of direct health care costs. Health care usage data will also be collected using a case report form (CRF) to complement the ICES administrative data. If a variable is not available in an administrative database, the CRF will capture the variable and be included in the economic analysis using standard micro-level costing approaches. Health care usage variables that will be collected using the administrative databases and CRF are direct costs, including health care facility visits, hospitalizations, family doctor visits, specialist visits, tests and procedures, other health care services, and falls. The project leads will work with ICES scientists, a health economist, and an ICES Research Analyst. The administrative databases will be accessed once all of the clinical data has been collected.

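### The Adverse Event Form is completed only for events judged to be caused by the intervention, so the rate the steering committee monitors is pre-filtered and form-recorded events cannot be compared reliably between arms

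*Protocol article*

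**What the plan says.** Three statements in the protocol article, Oversight and Monitoring, belong together.

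- Recording: "If the adverse event is deemed to be the result of the intervention, an Adverse Event Form will be completed". No form is described for an event that is not so judged.
- Monitoring: "The steering committee will monitor the rate of adverse events". The committee meets every 6 months and includes all central study team members.
- Independent oversight: "Given that this trial presents minimal risks, we will not have a data monitoring committee".

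The section also names what may happen to participants: "it is possible that they might experience muscle stiffness, soreness, falls, or injuries".

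A second route of capture is described elsewhere. Under Health Care Usage, the administrative databases and the case report form are to supply "hospitalizations, family doctor visits, specialist visits, tests and procedures, other health care services, and falls". Under Outcomes, "Health care usage data will be collected during follow-up assessments only", that is, at 12, 24 and 36 weeks. Neither section attaches a causality condition or limits the collection to one arm.

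**The concern.** The usual order is to record an event and then judge whether it is related. Here the judgement comes first and decides whether the form exists. A wrong or inconsistent judgement then leaves no adverse event form behind, so it cannot be audited or revised later.

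Two things are at stake. First, the quantity the committee is said to monitor is an adverse event rate, but the only adverse event record described supplies a rate of attributed events. With no data monitoring committee, no other safety review is described. Second, the three programs differ in how staff meet participants, and therefore in how an event comes to notice and how readily it is linked to the program. If form counts were later set side by side by arm, a difference could reflect ascertainment rather than risk.

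**Working it through.** The plan gives no figure on this point, so the check sets the sections side by side and then shows how sensitive a form-based comparison would be.

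**1. Does the rule match the monitored quantity?** The form is conditional on attribution, while the monitored rate carries no such condition. The article does not say that the rate is computed from the forms, but it describes no other adverse event record. Health care usage data do not fill the gap during the trial: the administrative databases are opened only after clinical data collection ends, and the case report form data are described for service use and cost-effectiveness.

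**2. Does staff contact differ by arm?** From Interventions:

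- Stepping Up: 2 sessions × 1 h × 12 weeks = 24 h of live contact. One weekly hour is exercise and one is self-management, so exercise seen by staff is 1 h × 12 = 12 h. A physiotherapist monitors the exercise class.
- Chair-based yoga: 2 × 1 h × 12 = 24 h, led by a fitness instructor.
- Telephone coaching: a first call of 20–30 minutes, then weekly calls of about 10 minutes. Assuming 12 calls in all, 20 + 11 × 10 = 130 minutes to 30 + 11 × 10 = 140 minutes. Against 24 × 60 = 1,440 minutes, that is 130/1,440 = 9.0% to 140/1,440 = 9.7% of the class contact. No walking is described as observed, but each call is one-to-one with a physiotherapist.

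Both the amount of contact and the staff who would first hear of an event therefore differ.

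**3. What happens after week 12?** The scheduled contacts common to all arms are then the 24- and 36-week assessments, done by a physiotherapist blinded to allocation (Data Collection and Management). A blinded assessor who hears of a fall is poorly placed to judge whether an unknown program caused it. The rule as written makes the record depend on that judgement.

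**4. How far could form counts mislead?** Let n be participants per arm, p the true event risk (equal in two arms) and s the share of events that reach a form.

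Recorded events = n × p × s; apparent risk ratio = (p × s₁)/(p × s₂) = s₁/s₂.

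With n = 83 (Sample Size), and p = 20% and all shares assumed:

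| s in first arm | s in second arm | Recorded events | Apparent risk ratio |
|---|---|---|---|
| 80% | 80% | 13.3 v 13.3 | 1.0 |
| 80% | 50% | 13.3 v 8.3 | 1.6 |
| 80% | 20% | 13.3 v 3.3 | 4.0 |
| 50% | 80% | 8.3 v 13.3 | 0.63 |

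The ratio does not depend on p; at 10% or 30% true risk it is the same. The first row shows that equal shares leave the ratio unbiased and only make the counts too low. The last row shows that the bias can run either way. The documents do not say which row applies.

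**The case against.** The strongest reply has four parts.

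*Comparable safety data exist.* A reader might infer from the form rule that safety cannot be compared between arms at all. The documents do not support that. Falls, hospitalizations and visits are collected in every arm with no causality condition, and the Analysis section plans count models comparing hospitalizations and physician visits between groups. This part stands, and it confines the point to form-recorded events.

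*No direction is established.* A reader might also infer that events in the telephone arm will be under-counted because nobody watches the walking. That arm has a one-to-one physiotherapist call every week, which may elicit events better than a group class. The Limitations section itself expects difficulty in noticing a participant's problems online. Class participants, too, are unobserved for nearly all of their time. This part also stands.

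*No planned analysis uses the forms.* Between-arm safety is not among the stated objectives, so no primary or secondary result is harmed. That is true and limits the weight of the point. It does not answer the mismatch with the monitored rate.

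*The article is condensed.* Who judges causality, by what criteria, and how unrelated events are logged may well sit in the full protocol, and their absence here is not held against the plan. But the form's condition is a stated rule rather than an omission, and it sits beside a monitoring task that it does not serve.

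**Conclusion.** The point holds in a limited form. As written, the form rule turns the monitored adverse event rate into a rate of attributed events, and it makes form counts unsuitable for comparison between arms. The events most affected are soreness, stiffness and injuries that lead to no care, because the health care usage list does not name them. Falls, hospitalizations and visits remain comparable.

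The size of any distortion cannot be computed from the documents, and its direction is unknown. The ratios of 0.63 to 4.0 rest wholly on assumed recording shares and show sensitivity only.

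The conclusion rests on two assumptions: that the monitored rate is drawn from the forms, and that the rule is applied literally. If a fuller protocol already logs every event and treats relatedness as a separate item, only the article's wording needs correction. The primary outcome, sample size and efficacy analyses are untouched.

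**What to change.** 1. For the remaining follow-up, record every reported adverse event in all three arms regardless of cause, with relatedness as a separate field. A blinded assessor can then record an event without judging its cause.
2. During follow-up, give the steering committee the unfiltered rate pooled over arms. By-arm rates should wait, because the committee contains all central study team members while outcome assessors and analysts are to stay blinded.
3. At final analysis, report falls and hospitalizations from the case report form and administrative data by arm, from randomisation to 36 weeks, as the unfiltered safety comparison. State whether the falls item includes falls that led to no care; the article does not say.
4. Label the forms completed under the existing rule as events judged related, and do not present their counts as overall adverse event rates by arm.

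Recruitment closed in January 2025, so step 1 cannot reach back to randomisation for those already enrolled, and it helps only for whatever follow-up is left before October 2025. Steps 3 and 4 remain possible after that date, since analysis is due to begin in November 2025.

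The cost is one revised instruction, slightly more form completion until October 2025 and one extra table.

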### Ethical Considerations

This study has received final approval from the Hamilton Integrated Research Ethics Board (HiREB Project #10663). Participants will provide informed verbal consent to participate. Ongoing consent will be implied by continued involvement in the trial. Participants will be informed that they may withdraw at any time with the option of removing their data from the study by notifying study staff.

## Results

Recruitment for the trial concluded in January 2025 with a total of 253 participants enrolled. Data collection commenced in August 2021 and will be completed in October 2025. Data analysis will begin in November 2025 and results will be published in Summer 2026. Refer to Figure 2 for the CONSORT flow diagram. Data supporting this study will be openly available from the Open Science Framework repository [96].

**Figure 2 figure2:**
[figure not shown]
CONSORT (Consolidated Standards of Reporting Trials) flow diagram.

## Discussion

### Principal Findings

Approaching functional decline from a primary prevention perspective by targeting individuals with PCML is important. Online community-based mobility programs have the potential to reach large groups of older adults to improve quality of life and to maintain or enhance physical function [97]. Such programs may also translate to lower health care system costs [98]. There have been several other rehabilitation programs successfully delivered online with positive results, including a multicomponent rehabilitation program to frail older adults during the pandemic [99], a cardiac rehabilitation program [100], and stroke [101] and cancer [102] rehabilitation programs. A recent survey showed that 71% of the 184 pulmonary rehabilitation programs surveyed were delivered remotely [103].

### Limitations

There are some limitations that might be encountered during this trial. The delivery of the intervention virtually rather than in person may result in problems detecting when a participant is having difficulty and requires correction. The ability to provide individual tailoring or to determine if a participant has achieved mastery of an exercise will be challenging in an online group format since participants will be progressing at different rates and 1-1 interactions will disrupt the flow of an online class. To mitigate these issues, we will have the physiotherapist observing and providing feedback and tailoring recommendations to the participants at the end of the class.

### Conclusions

This trial will evaluate the impact of the Stepping Up program on walking speed, as well as on aerobic exercise capacity, dual-task cost, physical functioning (balance and strength), balance confidence, extent of community mobility, SM of mobility, and quality of life. We will also examine the cost-effectiveness of the STEPPING UP program. Results will establish if this evidence-based initiative, which has modest resource demands, has the potential to serve as a model for sustainable, accessible, and cost-effective programming for individuals with early mobility limitations.

## Appendix

Multimedia Appendix 1 SPIRIT (Standard Protocol Items: Recommendations for Interventional Trials) checklist.

Multimedia Appendix 2 Interview guide.

## Abbreviations

4MGS: Four-Meter Gait Speed
CRF: case report form
ICC: intraclass correlation coefficient
ICES: Institute for Clinical Evaluative Sciences
IPAQ: International Physical Activity Questionnaire
MAT-sf: Mobility Assessment Tool-Short Form
MCID: minimally clinically important difference
PCML: Preclinical mobility limitation
QALY: quality-adjusted life year
RC: research coordinator
RCT: randomized controlled trial
REDCap: Research Electronic Data Capture
SM: self-management
SPIRIT: Standard Protocol Items: Recommendations for Interventional Trials
TOML: task-oriented motor learning
TUG: Timed Up and Go
YMCA: Young Men’s Christian Association
